## Methods/Design

### Participants

The Institutional Review Board at Wills Eye Hospital approved the study procedure, which was conducted in accordance with the Declaration of Helsinki. Informed consent was obtained from all participants. The consent was in accordance with Health Insurance Portability and Accountability Act (HIPAA) regulations.

Investigators in the Glaucoma Research Center reviewed the electronic medical records of patients being cared for by the Glaucoma Service of the Wills Eye Hospital to identify eligible patients.

One hundred sixty-one (161) patients are enrolled in the study. Patient eligibility is determined according to the inclusion and exclusion criteria specified in Table 1.

**Table 1 Tab1:** Inclusion and exclusion criteria for patient enrollment

Inclusion criteria	
• Minimum 2-year diagnosis of primary open-angle glaucoma, primary angle-closure glaucoma or pseudoexfoliation glaucoma	
• Disc Damage Likelihood Scale stages 5 through 8 in at least one eye with characteristic visual field loss	
• Age between 21 and 85 years	
• Able to understand and speak English	
Exclusion criteria	
• Unlikely to be available for annual ocular examination and reassessment across a 4-year period	
• Neurological or musculoskeletal diseases, including dementia that would influence performance on activities of daily living	
• Incisional eye surgery within the past 3 months	
• Laser therapy within the previous month	
• Any cause for visual impairment other than glaucoma	
• Any medical condition which in the investigator’s opinion would preclude the patient from providing reliable and valid data (e.g., cognitive impairment)	

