### Statistical analysis and sample size justification

*Primary Outcome Variables* will be divided into three groups: 1) QoL (NEI-VFQ-25 and MGSS) 2) performance-based measures of visual function (CAARV) and 3) Clinical measures of vision (better and worse eye VF mean defect, better and worse eye VA, and binocular SPARCS contrast sensitivity). *Primary Exposure/Demographic Variables* will be characterized as baseline DDLS score, age, ethnicity, gender, type of glaucoma, and number of medical comorbidities. *Secondary Variables* will be characterized as better and worse eye IOP, treatments, and duration of treatment.

All primary and secondary variables measured at baseline will be compared using means, medians, standard deviations, ranges or frequencies, and percentages. At baseline, Spearman correlation coefficients will be provided for all pairs of outcome variables and demographic variables.

In order to characterize the longitudinal trajectory of VRQoL, clinical measures of vision, and vision-related functioning over a 4-year period, analysis of these outcomes will proceed in two stages. First, mixed effects linear regression will be used to model the average trajectory of the sample. This will identify the appropriate parametric forms for each outcome trajectory. The study collects outcomes at five different timepoints over the 4-year study period. Linear and quadratic curves will be calculated, as well as a saturated model that treats time as a categorical explanatory variable. This allows for estimation of the mean outcome score for each visit. The mixed effects model will account for correlation among repeated measurements from the same patient. Our goal in these analyses is to identify the most parsimonious model that adequately represents the shape of the outcome trajectory over time. Ideally, a linear model will be sufficient. It is possible, however, to imagine scenarios where a quadratic term may be required (e.g., initial decline followed by stabilization).

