Second, because glaucoma is a disease with much subject heterogeneity, there are likely to be patients that differ from others in their experienced trajectories. MPlus software will be used to implement Growth Curve Mixture Modeling (GCMM) [30, 31]. This will group patients into a finite number of latent classes characterized by differing outcome trajectories over time. The model contains two parts: 1) the outcome model (i.e., the shape of the trajectory within each class), which is a mixed effects linear regression model and 2) the class probability model, which links the probability of being in any class with baseline exposure and demographic variables through a logistic regression model. Results from the initial mixed effects linear regression analysis will guide selection of the trajectory shapes for the GCMM. Results from the logistic regression portion of the model will allow for identification of baseline characteristics associated with differing changes in outcomes over time. Models will be fit with up to five latent classes using the Bayesian Information Criterion (BIC) to select the best-fitting model [32].

In order to determine whether changes in VRQoL are associated with changes in clinical measures of vision and performance-based measures of visual function, an extension of GCMM will be used to model to simultaneously model multiple outcome trajectories and identify classes based on the joint consideration of multiple outcomes. This will jointly model the trajectories of the primary outcome variables [32]. The resulting classes will have differing trajectory shapes for each outcome. Based on these results, we will be able to characterize the ways in which these outcomes change concurrently over time and the baseline patient characteristics that are associated with differing trajectories.

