No sample size formulae exist for GCMM. A sufficient sample size of 160 patients was chosen in order to identify subgroups using the latent class analysis. The primary goal of this analysis is to estimate parameters of the trajectory in each class with appropriate precision. The precision of the confidence interval will be calculated for the class- and outcome-specific slopes, assuming that a linear model is sufficient to describe the trajectory of a particular outcome. Class sizes will vary based on outcome. For illustration, we estimated precision for class sizes of 20, 60, and 100. Each patient will have up to five observations. Assuming 5 % dropout per year, the average number of observations per patient is 4.5.

Table 5 shows the width of the confidence interval for the slopes for NEI-VFQ-25 Total Score and LogMAR VA. For reference, a slope of one would indicate a 12-unit change in the NEI-VFQ over 12 months. A slope of 0.01 for LogMAR would indicate a change of 0.12 units over 12 months. The calculations given in Table 5 assume an intra-subject correlation of 0.2. Higher values within subject correlation would result in less precision while lower correlation would result in increased precision.

**Table 5 Tab5:** Sample confidence intervals for slopes of NEI-VFQ-25 and visual acuity

Number of subjects per class	Effective Sample Size N*4.5/(1 + (4.5-1)*0.2)	Distance from slope estimate to the two-sided 95 % confidence limits for the class-specific slope	
		NEI-VFQ (Std. Dev = 17)	LogMAR VA (Std. Dev = 0.2)
20	53	+/− 0.28	+/− 0.0033
60	159	+/− 0.16	+/− 0.0019
100	265	+/− 0.12	+/− 0.0014

*NEI-VFQ-25* National eye instate vision function questionnaire; LogMAR VA

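### The joint growth mixture model describes classes but names no estimate of the association between change in VRQoL and change in vision or function, which is the question it is meant to answer

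*Protocol article*

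**What the plan says.** All of this is in the protocol article, section on statistical analysis and sample size justification.

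- The aim is introduced as "In order to determine whether changes in VRQoL are associated with changes in clinical measures of vision and performance-based measures of visual function".
- The method for it is an extension of GCMM that forms classes on several outcomes together: "This will jointly model the trajectories of the primary outcome variables [32".
- The primary outcomes are "1) QoL (NEI-VFQ-25 and MGSS) 2) performance-based measures of visual function (CAARV") and, as clinical measures, "better and worse eye VF mean defect, better and worse eye VA, and binocular SPARCS contrast sensitivity". That makes three plus five, eight trajectories.
- Class membership is linked by logistic regression to "baseline DDLS score, age, ethnicity, gender, type of glaucoma, and number of medical comorbidities". Up to five classes are fitted and BIC chooses the number.
- What is to be read from the joint model is how the outcomes move concurrently in each class, and which baseline characteristics go with which class.
- On size, the section says that no formula exists for GCMM and then: "A sufficient sample size of 160 patients was chosen in order to identify subgroups using the latent class analysis". Table 5 gives the precision of a class-specific slope for one outcome at a time.

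The Participants section gives the number recruited: "One hundred sixty-one (161) patients are enrolled in the study".

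**The concern.** The question concerns an association within patients: does a patient whose vision declines faster also lose quality of life faster? The quantity that answers it is the correlation, covariance or regression of one slope on another. The article names none. Its Spearman correlations are taken at baseline only, and its single-outcome mixed models describe average trajectories.

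A set of class curves is not a substitute. Classes in a growth mixture are formed on intercepts and slopes together, so patients can be separated because they are worse on everything throughout, with no link between their rates of change. Correlated levels are plausible here, since four of the eight outcomes are better-eye and worse-eye versions of two measures. If classes that differ in severity were read as outcomes changing together, the aim would be answered wrongly. The Discussion presents the study of change in these relationships over four years as a major strength, so this is not a side question.

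**Working it through.** **1. The article's own figure.** Table 5 reproduces. Effective sample size is N × 4.5 / (1 + 3.5 × 0.2): 52.9, 158.8 and 264.7 for N = 20, 60, 100 (stated 53, 159, 265). The half-width is t(0.975, Neff − 2) × SD / (SD of visit time × √Neff). With visits at 0 to 48 months weighted 1, 0.95, 0.90, 0.85, 0.80 for dropout, the SD of time is 16.92 months. This gives 0.277, 0.157, 0.122 for NEI-VFQ-25 and 0.00326, 0.00185, 0.00143 for LogMAR, matching all six entries after rounding. The table is not in dispute, but it concerns one outcome in one class.

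**2. Parameter count for the joint model.** Inputs: 8 outcomes; linear shape, so 16 growth factors; K classes; covariance common to classes; 8 residual variances. The six baseline variables are assumed to need 7 coefficients (type of glaucoma taking two), plus an intercept, per non-reference class.

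Count = 16K + covariance terms + 8 + 8(K − 1).

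| Random-effects covariance (assumed) | Terms | K = 2 | K = 5 |
|---|---|---|---|
| Unstructured | 16 × 17 / 2 = 136 | 32 + 136 + 8 + 8 = 184 | 80 + 136 + 8 + 32 = 256 |
| Outcomes independent given class | 8 × 3 = 24 | 72 | 144 |
| Correlated intercepts only | 8 × 9 / 2 = 36 | 84 | 156 |
| Correlated intercepts, independent slopes | 36 + 8 = 44 | 92 | 164 |

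With 6 or 8 coefficients instead of 7, each count moves by 1 (K = 2) to 4 (K = 5). Quadratic shapes, which the article allows, take the unstructured count to 364 (K = 2) and 460 (K = 5). The comparison is with 161 patients.

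**3. Can levels alone produce classes?** Data were simulated from one population: 161 patients, 8 outcomes, 5 visits, no dropout, 20 data sets per setting. Growth mixtures were fitted without class covariates and BIC chose K. Slopes were uncorrelated across outcomes in the first four rows. The correlations are assumptions, because the article gives none between outcomes; the intra-subject correlation (ICC) of 0.2 is the article's own Table 5 value.

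| Level correlation | Slope correlation | ICC | Independent given class | Correlated intercepts, independent slopes | Unstructured |
|---|---|---|---|---|---|
| 0 | 0 | 0.6 | 1 class in 20/20 | 1 in 20/20 | 1 in 20/20 |
| 0.3 | 0 | 0.6 | 2 in 20/20 | 1 in 20/20 | 1 in 20/20 |
| 0.5 | 0 | 0.6 | 2 in 3, 3 in 17 | 1 in 20/20 | 1 in 20/20 |
| 0.5 | 0 | 0.2 | 2 in 19, 3 in 1 | 1 in 20/20 | 1 in 20/20 |
| 0.5 | 0.5 | 0.6 | 2 in 4, 3 in 13, 4 in 3 | 1 in 6, 2 in 14 | 1 in 20/20 |

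In the third row the spurious classes spanned about 1.5 outcome SD in level and about 0.07 SD per year in slope, or 0.07 × 4 = 0.28 SD over the study.

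**4. A model aimed at the question.** A bivariate linear growth model has 4 means, 4 × 5 / 2 = 10 covariance terms and 2 residual variances: 16 parameters, or 17 with a residual covariance. One of the 10 terms is the slope-slope covariance.

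**The case against.** The strongest reply is that the article does not fix the covariance structure. It says only that the within-class model is a mixed model, and a condensed article may leave the rest to an analysis plan that is not shown. Both the 184-to-256 count and the spurious classes therefore belong to specifications supplied for the check. That stands, and it rules out some stronger readings.

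- A reader might infer that the plan must either exceed its patient number or build classes from levels. It need not. Correlated intercepts alone stay below 161 with linear shapes, and correlated intercepts with independent slopes gave one class in every data set where slopes were uncorrelated.
- A reader might infer that the model will fail to converge. This is not shown. Parameters against patients is not an identification criterion, with about 161 × 8 × 4.5 = 5,796 outcome values, and the unstructured model recovered the single class in 20 of 20 sets in every setting. That check had no class covariates or dropout, so it does not prove stability either. The fit may be unreliable; no more can be said.
- A reader might infer that the joint model cannot estimate the association. An unstructured version contains slope-slope covariances. The fault is that the plan does not name or report them as the answer.

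It can also be said that authors who report class slopes would see near-parallel curves and not be misled. That is fair, but it relies on their judgement: the article states no rule for telling level classes from change classes.

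None of this supplies the missing estimate. The article itself chooses the method for this aim and says what will be read from it.

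**Conclusion.** The point holds in a limited form. The text alone shows the mismatch: the aim is an association between changes, and the declared output is a description of classes. That does not depend on any simulation or covariance assumption.

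Two supporting points are conditional. If outcomes are taken as independent given class and levels correlate at 0.3 to 0.5, BIC finds 2 or 3 classes in a single population with no slope association. If the covariance is unstructured, the eight-outcome linear model needs 184 to 256 parameters for 161 patients, and nothing in the sample size section supports a model of that scale. The article commits to neither structure.

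The matter is confined to this aim. The average-trajectory and single-outcome analyses are unaffected. It is an inexpensive improvement in method, not a reason to doubt the study as a whole.

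**What to change.** For this aim, pre-specify bivariate (parallel-process) linear growth models pairing NEI-VFQ-25 and MGSS in turn with CAARV, better- and worse-eye VF, better- and worse-eye VA, and SPARCS: 2 × 6 = 12 models. Name the slope-slope correlation with its 95% CI as the estimate.

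Keep the joint GCMM as an exploratory description. State its covariance structure, let random intercepts correlate across outcomes, and say in advance that classes differing mainly in level will not be read as concurrent change. Correlated intercepts do not make the number of classes meaningful by itself: when slopes were also correlated at 0.5, that model still split a single population in 14 of 20 sets.

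The cost is analysis-plan wording and a dozen small models on data already being collected, in the software already chosen. The downside is twelve pairwise results instead of one joint classification, some with wide intervals given at most five visits in 161 patients. They should be reported as estimates, not as twelve confirmatory tests.

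### Table 5 computes class-slope precision as if class membership were known, so it does not support the claim that 160 patients are enough to identify latent subgroups

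*Protocol article*

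**What the plan says.** The section Statistical analysis and sample size justification plans growth curve mixture modelling (GCMM), in which latent classes are formed from the outcome trajectories. The number of classes is left to the data: "Models will be fit with up to five latent classes using the Bayesian Information Criterion (BIC) to select the best-fitting model".

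On sample size the section first says "No sample size formulae exist for GCMM", then "A sufficient sample size of 160 patients was chosen in order to identify subgroups using the latent class analysis". It gives the aim as "The primary goal of this analysis is to estimate parameters of the trajectory in each class with appropriate precision". The supporting calculation is Table 5, introduced by "For illustration, we estimated precision for class sizes of 20, 60, and 100", with the half-width column headed "Distance from slope estimate to the two-sided 95 % confidence limits for the class-specific slope". For NEI-VFQ-25 the printed half-widths are 0.28, 0.16 and 0.12 points per month for 20, 60 and 100 patients. For LogMAR acuity they are 0.0033, 0.0019 and 0.0014.

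The section gives no expected slope difference between classes and no figure for the chance that a class is selected.

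**The concern.** Table 5 takes a class of a given size and asks how well its slope would be estimated. In a GCMM nobody knows who is in the class. Membership is inferred from up to five noisy scores per patient, and the class slope carries that uncertainty. Before that, BIC must prefer a model containing the class at all. Both steps depend on how far apart the classes are, and separation does not enter the table.

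The table therefore answers a different question from the one the sufficiency statement raises. A reader would take it that a class of 20 is resolved to within 0.28 points per month. If classes are only modestly separated, intervals may come out much wider than that. BIC may also return a single class, which could be taken as evidence that patients follow one common course.

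**Working it through.** **Inputs from the article.** SD 17 (NEI-VFQ-25) and 0.2 (LogMAR); intra-subject correlation 0.2; 4.5 observations per patient on average; visits at 0, 12, 24, 36 and 48 months; slope per month; two-sided 95%.

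**Reproducing Table 5.**

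- Effective sample size = N × 4.5 / (1 + 3.5 × 0.2) = N × 4.5 / 1.7, giving 52.9, 158.8 and 264.7 (printed 53, 159, 265).
- SD of visit times = √[(24² + 12² + 0 + 12² + 24²)/5] = √288 = 16.97 months.
- Half-width = t × SD / (√ESS × 16.97), with t on ESS − 2 degrees of freedom.
- NEI-VFQ-25: 0.276, 0.157, 0.121. LogMAR: 0.00325, 0.00185, 0.00143. These agree with the printed values to within one unit of the last digit.

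This is the slope formula for a group of known members. It has no term for class separation, misclassification or model selection.

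**Known membership under the table's own correlation.** With a constant correlation of 0.2 and complete data, the within-patient slope in 20 known patients has half-width 1.96 × 17 × √0.8 / √(20 × 1440) = 29.80 / 169.7 = 0.176, where 1440 is the sum of squared time deviations. Simulation gives 0.17–0.18 with complete data and about 0.19 with 5% annual dropout. The printed 0.28 is therefore conservative for known classes, which absorbs part of the loss from classification.

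**Latent membership.** Simulated: 160 patients, 20 declining and 140 stable, SD 17, correlation 0.2, equal baselines, one outcome, no covariates. Half-width is 1.96 × SD of the estimated small-class slope in a two-class fit. In the one-versus-two-class comparison the second class adds three parameters, so BIC requires twice the log-likelihood gain to exceed 3 × ln(160) = 15.2. The slope differences are assumptions.

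- A: random intercept and slope fitted, complete data; 600 replicates for half-width, 40 for BIC among one to three classes.
- B: random intercept fitted, 5% annual dropout; 150 replicates, one versus two classes.
- C: as B with a random slope also fitted; 100 replicates.
- D: random intercept fitted, complete data.

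| Slope difference per month (over 48 months) | Half-width (printed 0.28) | BIC selects the class |
|---|---|---|
| 0.25–0.28 (12–13 points) | A 0.57, B 0.57, D 0.50 | A 0%, B 1%, D 1% |
| 0.50 (24 points) | A 0.61, B 0.52, C 0.56, D 0.44 | A 0%, B 12%, C 0%, D 16% |
| 0.75 (36 points) | A 0.32, B 0.35, C 0.32, D 0.30 | A 28%, B 87%, C 42%, D 96% |
| 1.00 (48 points) | A 0.24, B 0.27, C 0.23, D 0.23 | A 93%, B 100%, C 93%, D 100% |

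The half-width fits in A, and the fits in B, C and D, included a start at or near the true classes, which favours recovery. Monte Carlo error in B and C is up to about 4–5 percentage points. For A's 28% the standard error is √(0.28 × 0.72 / 40), about 7 points.

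**Other conditions.**

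- Setting C at 0.75, with true slopes also varying within class (SD 0.15): 0.45 and 16%.
- Setting B with a class of 60 (printed 0.16): 0.52 and 2% at 0.28; 0.30 and 58% at 0.50; 0.17 and 100% at 0.75.
- Setting A at correlation 0.7: half-widths 0.44, 0.28, 0.16, 0.12 and detection 0%, 13%, 93%, 100% at 0.25, 0.5, 0.75, 1.0.
- Slope difference 0.5 plus a 10-point baseline difference: detection 69% with a random intercept only, 32% with a random slope also fitted.

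**The case against.** The strongest reply is that the simulated model is simpler than the planned one. The article plans baseline covariates in the class-probability model and an extension that forms classes from several outcomes jointly. At 0.5 points per month and correlation 0.2, with a random slope fitted, detection was 3% for one outcome, 45% for two and 95% for three. That assumes equal standardised separation in every outcome and independence given class, both favourable to the plan. One outcome with a covariate shifted by 1 SD gave 17%. This stands: the low detection rates describe single-outcome classes. Those are nevertheless the classes Table 5 addresses, since it is set out outcome by outcome.

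Second, the widest half-widths come from forced two-class fits in settings where BIC would seldom keep two classes, so they would seldom be published. This also stands in part. In setting B at 0.5 per month, among the 12% of runs where BIC did choose two classes, the half-width was still about 0.42, and the mean estimated decline was 0.59 against a true 0.50.

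Third, the article admits that no formula exists and calls its class sizes illustrative. That candour covers the class sizes, not the unstated assumption of known membership, and the absence of a formula does not support a claim of sufficiency. A condensed article may leave a simulation to the full protocol, so its absence is not the fault here. The fault is the printed claim and the column heading.

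A reader might go further and infer that the small-class precision is overstated throughout, or that BIC would usually miss a class of 20. The article does not support either, because it gives no slope difference. At 1.0 per month the printed precision is met and the class is nearly always found.

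**Conclusion.** Wrong as written, and worth correcting, but not a defect that undermines the study. Table 5 is a known-membership calculation presented as the precision of a latent class slope, and it gives no evidence that 160 patients are enough to find subgroups when BIC picks the number of classes.

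The consequence is conditional. For one outcome with correlation 0.2, equal baselines and no covariates, a class of 20 differing by about 0.5 points per month or less is estimated to within roughly 0.44–0.61 rather than 0.28, and is selected in about 0–16% of runs. At 0.75 the half-width is about 0.30–0.35, and detection runs from 28% to 96%, depending mainly on whether a random slope is fitted. At 1.0 there is no shortfall. Joint outcomes, informative covariates, baseline differences or a higher correlation could improve recovery; true slope variation within classes would worsen it. The first-stage mixed models do not depend on class recovery and are unaffected.

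**What to change.** Three changes to the sample-size text:

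1. Label Table 5 as *precision if class membership were known*.
2. Replace the sufficiency statement with the range of class sizes and slope differences that a short Monte Carlo study of the planned model shows can be recovered. Report the latent-class half-width and the BIC selection rate, for single outcomes and for the joint model, with the assumed correlation, random effects and dropout stated.
3. State that failing to select a small class is not evidence that no such class exists.

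The cost is a little simulation work in the software already planned and a less favourable stated precision for small, modestly separated classes. No extra patients or visits are needed.

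### Table 5 takes the precision of class-specific slopes from the design effect of a mean; under the correlation it assumes, the half-widths do not follow and the stated effect of correlation is reversed

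*Protocol article*

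**What the plan says.** In the protocol article, Statistical analysis and sample size justification, the target of the calculation is a slope: "The precision of the confidence interval will be calculated for the class- and outcome-specific slopes, assuming that a linear model is sufficient". For illustration, "we estimated precision for class sizes of 20, 60, and 100".

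Table 5 shows its method in a column heading, "Effective Sample Size N*4.5/(1 + (4.5-1)*0.2"), and reports the "Distance from slope estimate to the two-sided 95 % confidence limits for the class-specific slope". The outcome SDs stand in the column heads: "NEI-VFQ (Std. Dev = 17") and "LogMAR VA (Std. Dev = 0.2"). On the correlation the text says "The calculations given in Table 5 assume an intra-subject correlation of 0.2", and then "Higher values within subject correlation would result in less precision while lower correlation would result in increased precision".

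The same section plans mixed effects regression that accounts for within-patient correlation, followed by a growth mixture model whose within-class part is again a mixed effects model. The preceding section (Research instruments) sets assessments at baseline and at 12, 24, 36 and 48 months for every patient.

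**The concern.** The factor 1 + (m − 1)ρ inflates the variance of a mean of m correlated observations, or of the coefficient of a covariate that does not change within a patient. The slope over time is neither. Each patient is measured at several times, so the patient's own level largely cancels from the slope, and a shared intercept helps rather than hurts. What does hurt is variation between patients in the slope itself, and Table 5 has no term for it, although the article motivates the mixture model by heterogeneity between patients.

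The article says that no sample size formulae exist for the mixture model, and that precise trajectory estimates within each class are the main goal. Table 5 is therefore the only quantitative support for 160 patients. A reader who expects annual scores to be strongly correlated would conclude from the text that the slopes will be less precise than tabulated, when under the table's own correlation structure the opposite holds.

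**Working it through.** **Inputs from the article.** Visits at 0, 12, 24, 36 and 48 months. SD 17 (NEI-VFQ-25) and 0.2 (LogMAR), read as total SDs, as the design-effect formula implies. ρ = 0.2. N = 20, 60, 100. Dropout 5% of enrolled patients per year, so attendance is 100, 95, 90, 85 and 80%, which sums to 4.5 observations per patient. Slopes are per month.

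**Step 1: reproduce Table 5.**

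- Effective n = N × 4.5/1.7 = 52.9, 158.8, 264.7 (printed 53, 159, 265).
- Time SD, weighted by attendance: mean time 102/4.5 = 22.67 months; mean squared time 3600/4.5 = 800; SD = √(800 − 513.8) = 16.92 months.
- Half-width = t(0.975; n − 2) × SD/(√n × 16.92). For N = 20: 2.008 × 17/(7.276 × 16.92) = 0.277.
- NEI-VFQ: 0.277, 0.157, 0.122 (printed 0.28, 0.16, 0.12). LogMAR: 0.00326, 0.00185, 0.00143 (printed 0.0033, 0.0019, 0.0014).

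Every cell agrees after rounding. The table is an ordinary regression slope for independent observations, with n deflated by the design effect of a mean.

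**Step 2: slope precision under the same inputs.** With exchangeable correlation, complete data and a common slope within the class,

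Var(slope) = SD²(1 − ρ)/(N × Σ(t − mean t)²), with Σ(t − mean t)² = 576 + 144 + 0 + 144 + 576 = 1440.

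For N = 20: 1.96 × √(289 × 0.8/(20 × 1440)) = 0.176. The variance factor is 1 − ρ = 0.8 where the table uses 1.7; √(1.7/0.8) = 1.46.

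Generalised least squares (GLS) with monotone dropout (5% of patients with 1, 2, 3 and 4 visits each, 80% with all 5), using 1.96:

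| N | NEI-VFQ, printed | NEI-VFQ, GLS | LogMAR, printed | LogMAR, GLS |
|---|---|---|---|---|
| 20 | 0.28 | 0.188 | 0.0033 | 0.0022 |
| 60 | 0.16 | 0.108 | 0.0019 | 0.0013 |
| 100 | 0.12 | 0.084 | 0.0014 | 0.0010 |

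On these assumptions the printed values are 1.4 to 1.5 times the GLS values.

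**Step 3: direction of the correlation effect.** NEI-VFQ, N = 20, exchangeable correlation, same dropout:

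| ρ | GLS half-width | Table 5 formula (with 1.96) |
|---|---|---|
| 0 | 0.208 | 0.207 |
| 0.2 | 0.188 | 0.270 |
| 0.5 | 0.150 | 0.343 |
| 0.8 | 0.096 | 0.403 |

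The two agree at ρ = 0 and then move apart in opposite directions.

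**Step 4: the missing term.** The article gives no within-class slope SD, so the values here are assumptions. The random slope is added to the Step 2 model with time measured from baseline; ρ = 0.2, NEI-VFQ:

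| Slope SD per month | N = 20 | N = 60 | N = 100 |
|---|---|---|---|
| 0 | 0.188 | 0.108 | 0.084 |
| 0.4 | 0.267 | 0.154 | 0.119 |
| 0.5 | 0.301 | 0.174 | 0.135 |
| 0.8 | 0.417 | 0.241 | 0.187 |

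The printed half-widths are met at a slope SD of about 0.40 to 0.44. Below that they are too wide; above it, too narrow. At each slope SD tried, a higher ρ still narrows the interval.

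**The case against.** Four points can be made for the article.

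- *The table may be about right in size.* With a within-class slope SD near 0.4 to 0.5 per month, the GLS half-width at N = 20 is 0.27 to 0.30, close to the printed 0.28. This stands. A reader might infer from Step 2 that the printed values are simply 1.4 to 1.5 times too wide, but that holds only with no slope variation within a class, which the article neither states nor rules out. Agreement at one undeclared slope SD is coincidence, however: the table contains no such term.
- *Nothing depends on the table.* It is illustrative, no precision target is set, and 161 patients are already enrolled. The estimates and intervals will come from the fitted models. This stands and limits the severity. A reader might also infer that 160 patients are too few; the document does not support that, because there is no threshold to miss and, without slope variation, the error is conservative.
- *The direction depends on the correlation structure.* Under first-order autoregressive correlation the N = 20 half-width is 0.208, 0.221, 0.225 and 0.179 at ρ = 0, 0.2, 0.4 and 0.8, so a modest rise in correlation can cost precision. This stands against any unconditional claim that higher correlation helps. It does not rescue the sentence: the table's formula implies exchangeable correlation, the autoregressive effect is not monotone either, and none of these values reaches 0.28.
- *Large discrepancies at high correlation are hypothetical.* At ρ = 0.8 the table's formula gives about four times the GLS value (0.403 against 0.096), but the article prints figures only for ρ = 0.2. That comparison illustrates the direction; it is not the size of an error in Table 5.

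**Conclusion.** The point holds in a limited form. Table 5 uses a variance factor that does not apply to a slope over time, and the sentence on correlation is reversed under the exchangeable structure that the table's formula implies.

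The size of the error in the half-widths is known only conditionally. It is a factor of 1.4 to 1.5 too wide if patients in a class share one slope; it is close to nil at an assumed slope SD of about 0.40 to 0.44 per month; and the printed values are too narrow beyond that. All of these figures treat class membership as known, whereas the planned classes are latent, so none of them is the full precision of the mixture analysis.

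This is a should-fix correction to a stated precision. It is not evidence against the sample size.

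**What to change.** - Delete the effective-sample-size column.
- Recompute the half-widths by GLS for the planned mixed model, with the 5% per year dropout pattern, over a stated range of ρ (for example 0.2 to 0.8) and a stated range of within-class slope SD. Name the time origin for the random intercept, because the result depends on it once slopes vary.
- Label the table as conditional on known class membership.
- Replace the sentence on correlation with: *Under an exchangeable (random-intercept) correlation, higher within-subject correlation increases the precision of the slope; greater between-patient variation in slopes within a class decreases it.*

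The cost is one recalculated table and one sentence. Enrolment, data collection and the planned models do not change.
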